#### Intervention

A multifaceted strategy was chosen based on the consistent evidence that the most successful KT interventions tend to be interactive and multifaceted [3,10,11,14,15,46-49]. Systematic reviews of single interventions such as audit and feedback [50,51], reminders (*i.e.*, tools to aid decision-making and/or prompt a clinical action) [50], and opinion leaders [52] have also demonstrated some effectiveness in changing professional practice. As described below, we tailored our KT intervention to fit within the existing operational and organizational culture of each LTC home.

#### Target audience

The target audience of the multifaceted intervention is the Professional Advisory Committee (PAC), an interdisciplinary team [53] that meets quarterly to address resident care and quality improvement objectives. Members of the committee typically include: the Administrator, Medical Director, Director of Care, Consultant Pharmacist, Director of Food Services/Dietician, and other nursing, medical or rehabilitation staff. In addition to PAC team members, all physicians responsible for the care of residents within the LTC home are invited to the sessions and are eligible for continuing medical education credits with the Ontario College of Family Physicians.

#### Development and piloting the intervention

The multifaceted intervention was developed and piloted in consultation with the PAC team at a local LTC home. This home identified several procedural and organizational barriers that we addressed in the final version of our modules and materials. Learning modules and materials were built around a toolkit (including DVD, posters, panel cards, case studies) we developed for the *Ontario Osteoporosis Strategy in LTC* (http://www.osteoporosislongtermcare.ca[54]) in consultation with stakeholders. Materials were based on a research synthesis on hip fracture prevention strategies in LTC [22] and incorporate the 2010 Osteoporosis Canada Clinical Practice Guidelines [21].

#### Multifaceted intervention components

As outlined in Figures 1 and 2, intervention homes take part in three interactive educational sessions, approximately six months apart. To maximize participation, these sessions are delivered during a regularly scheduled meeting of the PAC team. An expert opinion leader facilitates the first two interactive educational sessions (approximately 45 to 60 min in length) via webinar technology, with the study coordinator on-site to facilitate and distribute materials. A Geriatric Nursing Consultant leads the third session (approximately 30 min) via webinar. The key components of the multifaceted intervention (Table 1) are:

1. Expert opinion leader: Utilizing the framework by Locock *et al.*[55], we define an expert opinion leader as ‘a credible authority (often an academic or consultant) able to explain the evidence and respond convincingly to challenges and debate.’ Such a person is distinct from a peer opinion leader who may be more influential as a role model in daily practice. The expert opinion leader may be particularly valuable in the initial stages of implementing change by ‘translating it into a form which is acceptable to practitioners and takes account of their local experience’ [55]. In our study, the expert opinion leaders are physicians specializing in osteoporosis and/or geriatrics who are active in national/international research and guidelines development.

2. Learning modules: At each session, a learning module is presented and there is opportunity for discussion and active participation. In brief, the first module introduces the study and materials, reviews best practices for OP management and fracture prevention, and provides an orientation to action planning for quality improvement. The second module emphasizes integration of osteoporosis and fracture prevention into care processes, reviews barriers and facilitators, shares strategies from other intervention homes, and provides a case-study exercise. The third module reviews accomplishments and action plan progress, provides information on hip protectors, identifies internal champions, and discusses post-study sustainability including an orientation to resources on our website (http://www.osteoporosislongtermcare.ca[54]).

3. DVD: At the first interactive educational session, the 10-minute ‘Meeting the Challenge of Osteoporosis and Fracture Prevention’ DVD is viewed, and a copy is left at the LTC home so that other staff and residents/families can be educated (available at http://www.osteoporosislongtermcare.ca[54]).

4. Performance reports (audit and feedback): Aggregate/facility-level data for vitamin D, calcium, and osteoporosis medication prescribing are presented in a graphical format at each interactive educational session. Reports are based on the previous month’s prescribing and are benchmarked against other ViD*OS* intervention homes. Confidential, individual performance reports are also provided to each physician.

5. Reminders/Point-of-care tools are distributed and discussed in the educational sessions. These tools include the process indicator checklist, treatment alert, and x-ray requisition stamp (summarized in Table 1). Tools were developed in consultation with the pharmacy provider, the *Ontario Osteoporosis Strategy in LTC*[54] steering group, and our pilot LTC home.

6. Action planning: This quality improvement component is built around the plan-do-study-act (PDSA) cycle [56,57]. In brief, the PDSA process engages teams in planning and managing change by breaking goals into manageable chunks, testing ideas and assessing the results in order to better monitor the impact of changes. Some LTC homes may be familiar with the PDSA process from the ‘Long-Term Care Best Practices Initiative’ [12]. After the learning module is presented, PAC teams discuss and complete an action plan work-sheet at sessions one and two to address barriers and identify organizational strategies, process changes, and specific action items for team members. Teams work on implementing action plans and progress is reviewed at the next session. Strategies generated from sessions are shared with other LTC homes.

7. Internal Champions: The concept of an internal champion is introduced at the first session. By the end of the study it is anticipated that each home will have an internally nominated champion, such as the consultant pharmacist and/or Director of Care. Champions will be linked by a forum on our website (http://www.osteoporosislongtermcare.ca[54]) to facilitate the ongoing sharing of experiences in implementing evidence-based changes in processes of care after the study is completed. Previous studies have found that the sharing of practical tips among LTC homes is useful in the implementation of protocols to improve processes of care [58].

**Figure 2 F2:**
[figure not shown]
Timeline of Data Collection and Sessions.

**Table 1 T1:** **Key Components of the Multifaceted ViD *****OS *****intervention**

Interactive Educational Sessions	Presentation of three learning modules that include a summary of best practices, special considerations for assessing/treating the elderly, key messages, integration of OP/fracture prevention into care processes, and a case study. Opportunity for discussion and active participation via problem-based learning and completion of action plans.
Expert Opinion Leader/ Study Coordinator	Expert opinion leader leads first and second interactive educational sessions via webinar (with study coordinator facilitating on-site). A Geriatric Nursing Consultant leads the third interactive educational session via webinar.
DVD	A 10-min DVD, ‘Meeting the Challenge of Osteoporosis and Fracture Prevention,’ is viewed at the first interactive educational session (and a copy left for the team to educate other/new staff members, residents, families). This DVD was created by the * Osteoporosis Strategy for LTC* (http://www.osteoporosislongtermcare.ca[54]) and is specific to the LTC context.
Performance Reports (Audit and Feedback)	Performance reports for vitamin D, calcium, and osteoporosis medications prescribing (aggregated for all residents in a home) and benchmarked against other ViD*OS* intervention homes, are presented at each interactive educational session. Confidential, individual performance reports are also provided to each physician.
Reminders/Point of Care Tools	Treatment Alert: A tool used by consultant pharmacists to alert physicians and nurse practitioners to assess and consider osteoporosis treatment for residents at increased risk for fracture (based on the 2010 Osteoporosis Canada Clinical Practice Guidelines [21].
	X-ray Requisition Stamp: A stamp labeled ‘please rule out vertebral fractures’ to add to chest X-ray requisitions.
	Process Indicator Checklist: This tool assists teams with creating internal processes and policies that support and sustain appropriate prescribing and other osteoporosis and fractures best practices (*e.g.*, admission/quarterly assessment, diagnoses documentation, ongoing staff education and training).
Action Planning for Quality Improvement	Discussion/completion of a work-sheet to set specific action items for team members, address barriers and facilitators, and outline best practices strategies. Homes work on action plans between study sessions.
Internal Champion	A PAC team member, such as consultant pharmacist and/or Director of Care, who will network with champions at other LTC homes (via online forum http://www.osteoporosislongtermcare.ca[54]) and continue to promote best practices after the research team has left.
Tool-kit*	The tool-kit includes: the 10-min DVD (‘Meeting the Challenge of Osteoporosis and Fracture Prevention’), informational pocket cards, case studies, and posters. Distributed to all LTC homes as part of the *Ontario Osteoporosis Strategy for LTC*.
Osteoporosis Long-Term Care Website*	The website (http://www.osteoporosislongtermcare.ca[54]) with an interactive forum for Internal Champions, is promoted to all LTC homes via the *Ontario Osteoporosis Strategy for LTC.*

#### Control homes

Control homes will receive no intervention. After the intervention homes have completed the study, the control group will have the option of attending a group webinar that presents a summary of key messages from educational modules. They will also be provided with an opportunity to appoint an internal champion who will receive post-study resources and updates. All LTC homes (control and intervention) will also have the opportunity to access continuing education through professional meetings (*e.g.*, the Ontario Long-Term Care Association and the Ontario Long Term Care Physicians).

#### LTC osteoporosis toolkit and website

Both control and intervention homes received the LTC Osteoporosis Toolkit in 2009/2010, which includes a 10-minute DVD, ‘Meeting the Challenge of Osteoporosis and Fracture Prevention,’ pocket cards, case studies, and posters. This toolkit was distributed to all Ontario LTC homes as part of the provincial government-funded *Ontario Osteoporosis Strategy*[59]. The toolkit was developed to increase awareness of best practices for osteoporosis and fracture prevention. An introductory group webinar was available to all LTC homes in Ontario to introduce the toolkit components. In late 2011, the *Ontario Osteoporosis Strategy for LTC* website (http://www.osteoporosislongtermcare.ca[54]) was launched and was promoted in all LTC homes across Ontario.

#### Post-study sustainability

The final phase of the knowledge to action (KTA) cycle [60] includes building sustainability mechanisms into the intervention. It is anticipated that implementation of osteoporosis best practices will continue through the work of each LTC home's internal champion, who will be provided with updated resources and support by a forum on our website (http://www.osteoporosislongtermcare.ca[54]). This will enable the internal champions to interact with each other and share successes and challenges. We will work with our partner pharmacy provider to distribute prescribing reports to LTC homes one year after completing the study. This feedback is important given the high turnover of residents in LTC resulting in a different cohort of residents and staff since the study began.

### Data collection

#### Facility-level

Feasibility data are collected by the study coordinator. Other facility-level data being collected include the number of resident beds, location/type of population centre (*i.e.*, small, medium, or large population centres as defined by Statistics Canada) [61], profit status (profit, non-profit), chain affiliation, and number of treating physicians at baseline.

#### Patient-level

Figure 2 provides an overview of the data collection time-line. De-identified clinical data including demographic, prescribing, and co-morbidities (from the Medication Administration Record) are collected from the pharmacy database by the Director of Systems Services at Medical Pharmacies ([name]).

Falls and fractures data for every resident are collected by a LTC staff member at each home for three-month periods at three times during the study (coinciding with prescribing data pulls, Figure 2). The information source used to populate the data collection spreadsheets may vary by LTC home and sources are documented by the study coordinator. With the recent wide-scale implementation of the RAI-2.0 assessments across Ontario LTC homes [34,35], future studies collecting information on falls and fracture data will likely use this as a data source. The RAI-2.0 is a standard assessment using common methodology and measures and is completed by trained assessors (typically within 14 days of admission and then on a quarterly basis).

#### Qualitative data

After intervention homes have completed the study, individual interviews will be conducted with selected participants to better understand their experience with the intervention. A research assistant (not affiliated with the study) will conduct interviews with two PAC team members (physician and the Director of Care or consultant pharmacist) at approximately seven to ten intervention home sites. Organizational changes to policies and processes in intervention homes will be measured by surveying the Directors of Care regarding the number of items on the process indicator checklist (Table 1) they initiated during the study and by examining changes captured in the action plans.

#### Trial management

The coordinating centre for the study is at McMaster University. The study coordinator and research assistants are responsible for submitting research ethics applications, scheduling of homes, travel arrangements, developing presentations, obtaining and storing consent forms, tracking and recording all decisions and transformations of data made throughout the investigation, and budgeting. All databases are password protected and kept on a secure network system.

#### Data monitoring

No formal comparison between control and intervention homes will occur until the end of the study when final analyses are performed. In accordance with Food and Drug Administration recommendations [62], because the elderly are considered a ‘potentially fragile population,’ a Data and Safety Monitoring Board (DSMB) with expertise in geriatric medicine and clinical trials research will meet to monitor ongoing trial processes. There are no formal stopping rules because the intervention is targeted at health professionals (*i.e.*, does not intervene directly with residents) and because the study is primarily designed to assess feasibility.

#### Blinding

Study participants, personnel, expert opinion leaders, and the analyst who provides the audit and feedback reports are not blinded to home allocation status. The outcome assessor ([name]) who downloads the demographic, prescribing, and co-morbidity data and the analyst who performs the final data analysis will be blinded to home allocation status. The staff members within each LTC home who are recording falls and fractures data are not blinded.

### Data analysis

#### Quantitative analysis

Data from the trial will be analyzed and reported in accordance with the CONSORT criteria [41,63,64]. The baseline characteristics will be reported as mean (standard deviation) or median (minimum, maximum) values for continuous variables and as counts (percent) for categorical variables. The primary feasibility outcomes will be analyzed using descriptive statistics expressed as percent and corresponding 95% confidence intervals (CI). Our primary analyses will be performed using the intention-to-treat principle. The generalized estimating equations (GEE) technique, assuming an exchangeable correlation structure [65], will be used to determine differences between groups for the proportion of residents prescribed vitamin D, calcium and other osteoporosis medication, and number of fractures or falls. The GEE method will take into account the clustered nature of the data, given that residents treated within a LTC home are expected to be similar or correlated (clustered variable will be the LTC home). For the model, the unit of analysis will be the resident and the unit of inference will be the home. There is an increased risk of imbalance at the resident-level because of the home-level randomization. Therefore, resident baseline characteristics that will be included in this analysis are: age, gender, co-morbidities, and the number of prescribed medications. Unadjusted and adjusted odds ratios (OR) and corresponding 95% CIs will be reported. All statistical analyses will be performed using the SAS/STAT 9.2 software package (SAS Institute Inc., Cary, NC, USA) with the criterion for statistical significance set at α ≤0.05.

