## Methods

### Study population

The Vitamin D and Osteoporosis (ViD*OS*) study is currently underway in 40 LTC homes (19 intervention and 21 control) in Ontario, Canada. In Canada, LTC homes (also known as nursing homes or homes for the aged) are government-regulated facilities designed for individuals who require onsite nursing care, 24-h supervision, or personal support [36]. Our recruitment strategy included LTC homes located in communities of all sizes and geographical regions across the province of Ontario.

In order to make this study as generalizable as possible, we have only two facility-level eligibility criteria, and no patient-level criteria. All LTC homes serviced by our partner pharmacy provider (Medical Pharmacies Group Limited) and who have more than one prescribing physician (at the time of recruitment) were eligible for recruitment into the study. Medical Pharmacies is a large pharmacy provider whose services include medication packaging and distribution, clinical support, and consulting services to approximately one-third of all LTC homes in Ontario. Our rationale for excluding LTC homes with only one treating physician is to maintain anonymity during the presentation of prescribing reports at educational sessions. Furthermore, the requirement of having at least two physicians per home decreases sample size as it contributes to a lower intracluster correlation coefficient [37].

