#### Randomization and consent

Stratified block randomization was used to randomly allocate LTC homes to the intervention or control arm of the study (recruitment is now closed). LTC homes were stratified based on home size and profit/non-profit. Profit status was taken into consideration because there is some evidence that the quality of care is higher in non-profit homes compared to for-profit homes [43-45]. The allocation sequence was computer generated using nQuery 6.0 software by an off-site research member who is not involved in the recruitment, enrollment of clusters, or data analysis. Once the appropriate representative from the home was consented, the independent member assigned intervention and control groups based on the sequence and notified the coordinating centre. Because the homes are not blinded to treatment arms, the homes were informed of their allocation.

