#### Sample size

Our sample size was calculated to detect a difference in the percentage of residents prescribed ≥800 IU/daily vitamin D at follow-up in the intervention versus control groups. We assumed an average of 120 residents per LTC home and that 30% of residents were prescribed ≥800 IU/daily vitamin D at baseline [33]. We postulate a 20% increase in vitamin D prescribing in the intervention group and a 5% increase in the control group (to account for the potential impact of other province-wide initiatives such as the *Ontario Osteoporosis Strategy for LTC*). Based on these assumptions, to detect a 15% difference in prescribing between the groups with an intracluster correlation of 0.10 (two-sided test with significance = 0.05), a sample size of 2,160 residents from 18 LTC homes in each of the intervention and control groups is required to achieve 82% power. Factoring in a potential 10% dropout rate, the recruitment target was 40 LTC homes (20 = intervention, 20 = control).

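### With 36 to 40 homes and no small-sample method named, the planned GEE test of the primary vitamin D outcome would run at about 6 to 7% instead of 5% if the usual robust variance with normal quantiles is used

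*Protocol article*

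**What the plan says.** Under Quantitative analysis the method is fixed as follows: "The generalized estimating equations (GEE) technique, assuming an exchangeable correlation structure [65], will be used to determine differences between groups". The same section says that the "clustered variable will be the LTC home", that the resident is the unit of analysis and that the home is the unit of inference. Unadjusted and adjusted odds ratios with 95% CIs will be reported from SAS/STAT 9.2, "with the criterion for statistical significance set at α ≤0.05". The adjustment set is at resident level: "resident baseline characteristics that will be included in this analysis are: age, gender, co-morbidities, and the number of prescribed medications".

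The number of independent units is small. Study population gives "40 LTC homes (19 intervention and 21 control"). Sample size requires "18 LTC homes in each of the intervention and control groups", that is 36 homes, "with an intracluster correlation of 0.10 (two-sided test with significance = 0.05"), and allows for 10% dropout from a target of 40.

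Under Randomization and consent, "LTC homes were stratified based on home size and profit/non-profit". Neither factor is listed as a model term.

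The article does not say whether the standard error is empirical, model-based or corrected, or whether the reference distribution is normal or t.

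**The concern.** The usual robust (sandwich) GEE variance, referred to a normal distribution, is justified when the number of clusters is large. An average of 120 residents per home does not supply that. What counts is the 36 to 40 homes. With so few, two things push the same way. The robust variance is biased downward because the residuals come from a fitted model. The normal quantile of 1.96 also ignores that the variance is estimated on only 34 to 38 degrees of freedom.

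At stake are the actual error rate of the primary clinical comparison at 6 and 12 months and the width of its intervals. The width matters even in a pilot, because the Discussion says that effect sizes and the intracluster correlation will inform later studies.

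**Working it through.** **Inputs from Sample size and Study population.** 120 residents per home; 35% (control) against 50% (intervention) at follow-up; ICC 0.10; two-sided 0.05; 18 homes per arm required; 19 and 21 homes randomized.

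**The plan's own power figure.**
- Design effect = 1 + (120 − 1) × 0.10 = 12.9.
- Effective n per arm = 2,160 / 12.9 = 167.4.
- SE of the difference = √[(0.35 × 0.65 + 0.50 × 0.50) / 167.4] = 0.0534.
- Power = Φ(0.15 / 0.0534 − 1.96) = Φ(0.85) = 80.2%. The stated 82% is reproduced to within 2 points.
- Dropout: 18 / 0.90 = 20 per arm, as stated.

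**Analytic check of the error rate (arm only, equal home sizes).** With k homes per arm the sandwich variance is smaller than the unbiased one by a factor (k − 1)/k. The true size is then P(|t| > 1.96 × √[(k − 1)/k]) on 2k − 2 degrees of freedom.

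| Homes per arm | SE ratio | df | Size, sandwich with 1.96 | Size, unbiased variance with 1.96 |
|---|---|---|---|---|
| 18 | √(17/18) = 0.972 | 34 | 6.5% | 5.8% |
| 20 | √(19/20) = 0.975 | 38 | 6.4% | 5.7% |

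The 19 against 21 split also gives 6.4%. The last column shows that the normal quantile alone accounts for part of the excess.

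**Interval width.** Corrected over uncorrected width = t quantile / (1.96 × SE ratio). At 18 per arm this is 2.032 / (1.96 × 0.972) = 1.067. At 20 per arm it is 2.024 / (1.96 × 0.975) = 1.060. The corrected intervals are therefore about 6 to 7% wider.

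**Simulation under the null.** Logistic GEE with exchangeable correlation, mean 120 residents per home. Runs without resident covariates used beta-binomial outcomes and 20,000 trials per setting (simulation error about 0.2 points). Runs with resident covariates used 8,000 trials (about 0.3 points).

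| Model, uncorrected sandwich with 1.96 | 36 homes | 40 homes |
|---|---|---|
| Arm only | 6.5–6.7% | 6.0–6.7% |
| Arm + four resident covariates | 7.0% | 6.8% |
| Two home-level terms (size, profit status) added | 7.4–7.6% | 7.2–7.5% |

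In the arm-only model the mean standard error was about 2 to 4% below the empirical standard deviation.

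**After correction (ICC 0.10, prevalence 35%).** Kauermann-Carroll variance with t quantiles gave 4.8–5.1% with no home-level covariate and 5.0–5.2% with two. The t quantile alone, without the variance correction, left 5.3–5.8% and 6.2–6.5%.

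**Power cost (18 homes per arm, arm only).** Noncentral t with noncentrality 0.15 / 0.0534 = 2.81 on 34 degrees of freedom gives 77.9% with the correction. The uncorrected test gives 81.5% and the normal approximation 80.2%. The loss is 81.5 − 77.9 = 3.6 points or 80.2 − 77.9 = 2.3 points, depending on the comparator.

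**Assumptions not in the documents.** Variation in home size (CV 0, 0.4 or 0.6), null prevalence, ICC values other than 0.10 (0.05 and 0.20 were also run), covariate distributions and effects, and a home random-effect SD of 0.65 on the logit scale in the resident-covariate runs.

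**The case against.** The strongest objection is that the uncorrected default is an inference from silence. The article fixes GEE, the working correlation, the cluster and the significance level. Nothing in it rules out a corrected variance or a t reference. Such detail is often left to an analysis plan, and that plan is not shown. This stands in part: the article does not state that uncorrected inference will be used, and a reader should not infer that it does. If the analysis plan already names a correction, the point is closed. If not, the method as written permits the inflated test, and a better one is available at small cost.

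A reader might also infer an error rate of 8 to 9% from the addition of home-level covariates. The documents do not support that. All listed covariates are resident characteristics, and the two stratification factors, entered as one term each, give only about 7.2 to 7.6%. Reaching 8 to 9% takes roughly three to four home-level terms.

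Finally, the trial is a pilot that emphasizes feasibility. That limits the consequence but does not remove it, because vitamin D prescribing is also a primary outcome and is tested at 0.05.

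**Conclusion.** The point holds in a conditional and modest form. If the usual robust variance with normal quantiles is used on 36 to 40 homes, the 5% test of the primary vitamin D outcome runs at about 6 to 6.7% unadjusted and about 7% with the four listed covariates. That is an excess of about 1 to 2 percentage points. The analytic and simulated results agree.

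The same sentence of the plan also governs the calcium, osteoporosis medication, falls and fracture comparisons. It is tempting to carry these figures over to them, but only a binary outcome at prevalences of 35 to 50% was examined. The size of the effect for fall counts, rare fractures and the smaller high-risk subgroup was not computed.

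**What to change.** Add one sentence to Quantitative analysis before the final comparison is made. It should say that all between-arm GEE tests and confidence intervals use a bias-corrected robust variance (for example Kauermann-Carroll) with t quantiles, on degrees of freedom equal to the number of homes minus the number of home-level parameters. With intercept and arm only, that is 36 − 2 = 34 or 40 − 2 = 38. If home size and profit status were entered as one term each, it would be 32 or 36. Both parts are needed, since the t quantile alone does not fully restore 5%.

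The cost is one sentence, a corrected-variance option or short macro in SAS, intervals about 6 to 7% wider, and roughly 2 to 4 points of power. Naming the method in advance also prevents a choice of variance estimator after the results are seen. If the analysis plan already contains such a statement, a cross-reference is enough.
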